### Outcomes

The primary outcome will be participation in the screening test, defined as return of the completed FIT within 12 weeks of the invitation. Secondary outcomes (stage of change, psychosocial variables and qualitative evaluation) will be collected via the baseline and endpoint surveys, and the qualitative evaluation. The data collected during each phase is summarized in Table 3.

**Table 3 T3:** Data collection phases and measures obtained

**Phase**	**Data collection**	**Measures**
Phase 1	Baseline survey mailed to psychosocial subgroup (n = 2,400); reminders sent 3 and 7 weeks from initial mailing	Demographic characteristics: age, education, country of birth, marital status, employment, insurance coverage.
		TTM stage: decision stage for screening assessed by TTM stage (precontemplation, contemplation, action, maintenance).
		Psychosocial constructs: barriers, benefits, self-efficacy, susceptibility, social influence and social support.
Phase 2	Screening advance notification and invitations; reminders sent 6 weeks after mailing of invitation	Receipt or non-receipt of completed FIT, date of return of FIT, reasons for opt-out recorded by the Bowel Health Service, Repatriation General Hospital, Adelaide, Australia.
Phase 3	Endpoint survey mailed to baseline survey respondents (n = 1,200, estimated); reminders sent 3 and 7 weeks from initial mailing	TTM stage and psychosocial constructs as measured in the baseline survey.
Phase 4	Qualitative evaluation; data obtained following screening phase from focus groups, including participants from each of the trial arms	Why participants chose or chose not to use the FIT.
		Reaction to, and satisfaction with, the intervention.
		How intervention materials could be improved.

*FIT*, fecal immunochemical test; *TTM*, transtheoretical model.

### Sample size considerations

Assuming a 50% return of the baseline survey, screening will be offered to a total of 8,000 participants (1,200 survey participants and 6,800 screening only participants). Participants who contact the research team and opt-out of screening due to: 1) recent FOBT screening; 2) recent colonoscopy; 3) recent bowel cancer diagnosis; or 4) medical condition that prevents the use of FOB-based screening tests, will be excluded from analysis on the basis that screening is not suitable/required for this group [3]. Those who opt-out of screening for reasons other than those listed previously (for example did not want to complete the screening) will be categorized as a non-participant for the purpose of analyses. Survey group participants who opt-out of the study prior to completing the endpoint phase will be excluded from analyses involving survey data.

Two participation rates will then be calculated for each trial arm: 1) inclusive of survey participants (2,000 per trial arm); and 2) exclusive of survey participants (1,700 per trial arm). Analyses will be conducted both with and without the inclusion of survey participants because participation for this subgroup is likely to be higher due to the baseline survey acting as a prompt for screening participation. Assuming a participation rate of at least 40% for the control group and allowing for up to 40% of invited participants to be excluded due to being up to date with screening [8], these group sizes permit the detection of differential FOBT uptake of at least 6% between any two groups with at least 80% power. A difference of at least 6% was considered by the research team to be the smallest difference that would be feasible to detect without requiring overly large sample sizes, and is similar to the effect size estimate used in our previous research [36].

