### Survey phases

Participants allocated to the survey group will be invited to complete a baseline behavioral survey prior to commencing the screening phase of the trial. Participants will receive a survey advance notification letter by mail, followed 2 weeks later by the survey package. Reminder letters will be mailed at 3 and 7 weeks to non-respondents. Data collection will cease at 12 weeks. Respondents will indicate consent to participate via return of the completed survey. Survey invitees will receive up to four letters inviting them to participate in the survey during the 12-week data collection period. No further attempts will be made to recruit non-respondents for either the survey, or the screening phase after this period on the basis that subsequent study invitations could be construed as harassment. This approach is consistent with previous population screening research utilizing electoral roll data [36]. Upon completion of the screening phase, baseline respondents will be invited to complete an endpoint survey via the same recruitment methods utilized for the baseline phase.

The baseline survey will collect demographic data (age, marital status, education, employment status, country of birth, language spoken at home and insurance status) and will obtain a baseline measurement for each of the psychosocial constructs targeted in the intervention (stage of readiness to screen, perceived barriers, benefits, social influence, social support, susceptibility and self-efficacy). Stage of readiness to screen will be measured using a staging algorithm utilized in previous research [36]. Each variable will be measured using a number of individual items and summed for an overall score. Response format for the psychosocial variables will be a five-point Likert scale ranging from ‘strongly disagree’ to ‘strongly agree’. It is anticipated that the surveys will take between 20 and 30 minutes to complete. Survey variables and example items are summarized in Table 1. The psychosocial measures and stage of readiness questions will then be repeated in the endpoint survey, in order to measure change from baseline to endpoint following exposure to the intervention.

**Table 1 T1:** Summary of variables included in the psychosocial survey and example items

**Variable**	**Items**	**Example**	**Reference**
Perceived barriers	11	A home stool test is embarrassing	Rawl *et al*. (2001) [37]

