### Statistical analyses

#### Primary outcome

A 2 x 4 (participation by intervention group) chi-squared test with alpha set at 0.05 will compare FIT participation rates between groups. Potential covariates such as demographic factors (age and socioeconomic status) and psychosocial variables (survey sample only) will be checked by the change in coefficient method using log binomial generalized linear models.

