#### Secondary outcomes

Change in psychosocial variables from baseline to endpoint will be calculated for the participants who complete both surveys. Change scores will be calculated by subtracting baseline from endpoint scores for each of the variables targeted by the intervention. These change scores will then be compared between intervention groups using analysis of covariance (ANCOVA), controlling for potential co-variation from demographic variables. Based on the predicted group sizes mentioned above, the ANCOVA using two-tailed significance will have 80% power to detect a difference of at least half a standard deviation for psychosocial variables between any two groups.

Qualitative data collected via telephone interviews will be analyzed using the framework analysis method recommended for applied health research by Green and Thorogood [45]. This method is suited to applied health research as it allows for the exploration of themes derived from *a priori* aims relevant to this research stage as well as emergent themes raised by respondents. The study will aim to recruit 20 screening participants and 20 non-participants for interview in order to achieve data saturation [45].

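### Survey-group men who leave the study before the endpoint survey are dropped from all survey-data analyses, including FIT participation models that need only baseline scores and FIT return

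*Protocol article*

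**What the plan says.** Four parts of the protocol article bear on this point.

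- **Sample size considerations** sets the rule: "Survey group participants who opt-out of the study prior to completing the endpoint phase will be excluded from analyses involving survey data". Just before it, men who decline screening for reasons other than the four listed ones (recent FOBT, recent colonoscopy, recent bowel cancer, unsuitable medical condition) are kept, and each such man "will be categorized as a non-participant for the purpose of analyses".
- **Statistical analyses, Primary outcome** plans participation models that use survey answers: "psychosocial variables (survey sample only) will be checked by the change in coefficient method using log binomial generalized linear models".
- **Statistical analyses, Secondary outcomes** has its own restriction. Change in the psychosocial variables "will be calculated for the participants who complete both surveys".
- **Survey phases** and **Outcomes** fix the timing. For the first survey, "Participants allocated to the survey group will be invited to complete a baseline behavioral survey prior to commencing the screening phase of the trial". For the second, "Upon completion of the screening phase, baseline respondents will be invited to complete an endpoint survey". The primary outcome is "defined as return of the completed FIT within 12 weeks of the invitation".

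The Participants section describes opting out as declining further contact from the study. It does not describe it as withdrawing data already given.

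**The concern.** The exclusion is worded by type of data (anything involving survey data), not by what an analysis needs. A survey-sample participation model needs a baseline score and a FIT result. Both can be available for a man who later leaves the study, and the rule still removes him.

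The removal depends on something that happens after randomization. A man who has no wish to screen may be more likely to ask not to be contacted again, so leaving may be related to the outcome. It may also be related to the letter, since a man can leave after reading it. Selection on the outcome raises the apparent participation rate in the survey sample. If it differs by arm, it distorts the arm effect.

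The covariate check is exposed in a further way. It compares the arm coefficient with and without a covariate. If the first fit uses all survey men and the second omits those who left, the coefficient can move through selection alone and be read as confounding.

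**Working it through.** **Inputs from the article.** 1,200 survey respondents offered screening in four equal arms, so 1,200 / 4 = 300 per arm. Control participation 40%; target difference 6 points; up to 40% of invited men excluded as up to date. The number of study opt-outs is not given, so every opt-out rate below is an assumption.

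**The plan's own figure.** The article claims at least 80% power for 40% versus 46% between any two arms. With a pooled-variance comparison of two proportions and two-sided alpha 0.05:

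- with survey men, 2,000 x 0.60 = 1,200 per arm gives 84.4%;
- without them, 1,700 x 0.60 = 1,020 per arm gives 78.2% (1,068 per arm would be needed for 80%).

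The figure is reproduced to within 2 points. It concerns FIT return only, so the exclusion does not enter it.

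**What each analysis needs.**

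| Analysis | Data needed | Covered by the exclusion as worded? | Exclusion needed? |
|---|---|---|---|
| 2 x 4 chi-squared test; two participation rates per arm | FIT return | No | No |
| Survey-sample log binomial models | Baseline survey, FIT return | Yes | No |
| Change-score ANCOVA | Baseline and endpoint surveys | Yes | No, already limited to completers |

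The added effect of the rule therefore falls on the middle row, where the data can exist.

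**Effect on the survey-sample rate.** Let p be true participation, a the opt-out proportion among men who return the FIT, and b that among men who do not. Then

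observed rate = p(1 - a) / [p(1 - a) + (1 - p)(1 - b)].

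Take p = 40% in both arms and a = 0. Each arm has 120 men who return the FIT and 180 who do not.

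- b = 10%: 120 / (300 - 18) = 120/282 = 42.6%
- b = 15%: 120 / (300 - 27) = 120/273 = 44.0%
- b = 20%: 120 / (300 - 36) = 120/264 = 45.5%

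A true null with b = 10% in one arm and 20% in the other shows as 2.9 points (ratio 0.455/0.426 = 1.07). With 10% and 15% it shows as 1.4 points. With the same b in both arms it shows as 0.

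**Other assumptions (a = 2%).**

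- The same b in both arms, at 5%, 10%, 20% or 30%: a true 40% shows as 40.7%, 42.1%, 45.0% or 48.3%, and the null difference stays 0.
- b = 20% in control and 10% in a targeted arm: a true null shows as -2.9 points (ratio 0.94), and a true 40% versus 46% (ratio 1.15) shows as 3.2 points (ratio 1.07).
- b = 10% in control and 20% in a targeted arm: the same true 6 points shows as 9.0 points (ratio 1.21).
- Equal b with a true 6-point effect: the ratio moves only slightly, from 1.15 to 1.144 at b = 10% and to 1.127 at b = 30%.

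**Precision.** Losing 10% of 300 leaves 270 per arm and multiplies the standard error by sqrt(300/270) = 1.05. Losing 20% leaves 240 and multiplies it by sqrt(300/240) = 1.12. For scale, the standard error of a difference at 300 per arm and 40% is sqrt(2 x 0.4 x 0.6 / 300) = 4.0 points.

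**The case against.** The strongest reply is that the sentence was probably written with the change scores in mind, that the number of men concerned may be small, and that the affected models are a covariate check in a subsample. All of that is plausible. The primary test and both planned participation rates use FIT return alone and are untouched. The article plans no survey-only participation rate, so 42.6% versus 45.5% shows what happens inside the models and is not an error in a planned result. The 2.9 points is also less than one standard error (4.0 points) and needs opt-out that differs by arm.

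Several stronger readings are tempting, and the article does not support them.

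- *That the exclusion contradicts the rule counting decliners as non-participants.* One sentence concerns opting out of screening, the other opting out of the study. A man who declines the FIT but stays in the study is a non-participant and is not deleted: the endpoint survey goes to baseline respondents, estimated in Table 3 at the full 1,200. The rules meet only for men who do both.
- *That the excluded men always leave after the letters and after the outcome is known.* The rule covers any exit before the endpoint phase is completed. Trial status puts the end of baseline collection in January 2013 and the screening offer in March 2013, so some men could leave before any letter.
- *That about half of the 1,200 men are lost.* That would need an assumed 50% endpoint return, and it would follow from the separate completers rule for change scores. Men who simply do not answer the endpoint survey are not described as opt-outs.
- *That completers-only change scores are an error.* They are a stated choice for a secondary outcome, and missing-data methods may be set out in an analysis plan that is not shown.

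What remains is that the text does not confine the exclusion to change scores. Since change scores already have their own restriction, the sentence has an effect of its own only where it is not needed.

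**Conclusion.** The point holds in a limited form. As worded, the rule deletes usable baseline and FIT data from the survey-sample participation models because of a post-randomization event that may be related to the outcome and possibly to the letter. It can bias the covariate-adjusted arm effects and reduces precision in a subsample of about 300 per arm.

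The size cannot be known from the article. Under the assumed opt-out of 10% versus 20% among non-participants, a true null appears as 2.9 points, about half the 6-point target. With equal opt-out a null difference stays at 0, although the participation level is still overstated when non-participants leave more often than participants. A reader might infer that the trial's primary result is biased; it is not. The matter is worth correcting because it is a stated rule, it serves no purpose in these models, and it is easily narrowed.

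**What to change.** Reword the exclusion so that it applies only to analyses that need endpoint survey scores. In the participation models, keep every baseline respondent offered screening and count study opt-outs with no FIT returned as non-participants. The four stated medical or up-to-date exclusions continue to apply, and data are dropped where a man withdraws consent to their use. Fit the models with and without each covariate on the same men, so that a shift in the arm coefficient cannot come from a change of sample.

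For the change scores, completers-only may stay as the main analysis. An optional sensitivity analysis could impute missing endpoint scores from arm, baseline scores, demographics and FIT return. It would rest on a missing-at-random assumption given those variables.

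The cost is a clause of text and, if the option is taken, one standard imputation run. No further data are needed. The participation models and the change-score analysis will then have different denominators, which should be reported.

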## Methods

### Study design

This study is a factorial design, RCT. A national sample of Australian men aged 50 to 74 years inclusive, will receive a free, mail delivered FIT, accompanied by either standard invitational materials (control), invitational materials modified to target psychosocial variables associated with stage of readiness to screen, or a combination of the standard and modified materials. The intervention will offer screening to participants consistent with the protocol utilized by the NBCSP, which includes a mailed advance notification letter, followed 2 weeks later by a mailed invitation letter and screening package. The content of the advance notification and invitation letters will differ by trial arm. The letters currently utilized by the NBCSP will serve as the control. The modified advance notification letter will be designed to target men in the precontemplation stage, while the modified invitation letter will target men in the contemplation stage.

Participants will be randomized to one of four trial arms of equal size (allocation ratio 1:1:1:1). Within each trial arm, participants will be randomized to a survey group, or a screening only group (allocation ratio 1:2.83). Participants in the survey group will complete behavioral surveys measuring the psychosocial variables targeted in the intervention, before commencing the screening phase (baseline) and again upon its completion (endpoint). Participants in the screening only group will receive the screening offer, without prior study engagement, consistent with the NBCSP. The use of behavioral surveys pre- and post-intervention will allow the study to examine the impact of the letters on the psychosocial variables they are designed to target. However, survey participation will be restricted to a survey subgroup because of the potential for completion of the survey to lead to increased screening awareness for this population.

Upon completion of the screening phase, a purposively selected subsample of participants in the screening only group will be invited to participate in semi-structured interviews to evaluate the intervention. The study design flow chart is shown in Figure 1.

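### The primary outcome is analysed with and without the survey men, neither analysis is named as decisive, and the pooled test takes no account of survey status

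*Protocol article*

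**What the plan says.** Under Outcomes, the protocol article defines one primary outcome: "The primary outcome will be participation in the screening test, defined as return of the completed FIT within 12 weeks of the invitation". No analysis set is attached to it.

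Under Sample size considerations, two participation rates per arm are planned, "1) inclusive of survey participants (2,000 per trial arm); and 2) exclusive of survey participants (1,700 per trial arm"), followed by: "Analyses will be conducted both with and without the inclusion of survey participants because participation for this subgroup is likely to be higher". The reason given is that the baseline survey may itself prompt men to screen. A single sentence then claims at least 80% power for both group sizes. Neither analysis is called primary, supportive or a sensitivity analysis.

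Under Statistical analyses, Primary outcome, there is one test and one alpha: "A 2 x 4 (participation by intervention group) chi-squared test with alpha set at 0.05 will compare FIT participation rates between groups". The section does not say which set the test uses. The covariates it mentions are age, socioeconomic status and, in the survey sample, psychosocial variables. Survey status is not mentioned.

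Under Study design, "Within each trial arm, participants will be randomized to a survey group, or a screening only group (allocation ratio 1:2.83"). Under Survey phases, men who do not return the baseline survey are not contacted again, for the survey or for screening. The survey men in the pooled analysis are therefore responders only.

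**The concern.** Two analyses of one primary outcome, both powered and neither ranked, leave the decision rule open. If they agree, nothing is lost. If one is significant and the other is not, the plan does not say which is the trial's answer, and the choice would be made with both results in view.

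The choice matters because the two sets answer different questions. The screening-only set reflects men approached as in the national programme. The pooled set mixes them with men who were prompted by a survey and who chose to return it. The plan itself expects higher participation in the second group, yet the pooled test treats all men as one homogeneous group per arm. When participation differs between the groups, the unstratified variance is larger than it need be.

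**Working it through.** **Inputs from the protocol article**
- Offered screening per arm: 1,700 screening-only men and, at 50% survey return, 300 survey men (half of 600).
- Exclusions: up to 40%, leaving 1,700 x 0.6 = 1,020 and 300 x 0.6 = 180, so 1,200 pooled.
- Control rate 40%, target difference 6 points, alpha 0.05.

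**Assumptions, because the article gives no figure**
- Survey men screen at 40%, 55% or 70%.
- Exclusions fall equally on both groups.
- The letter effect, in percentage points, is the same in both groups.

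**Step 1. The plan's own power figure (40% v 46%, two-sided 0.05).** Power = Φ[(0.06 − 1.96·s0)/s1], with s0 = √(2·0.43·0.57/n) and s1 = √((0.40·0.60 + 0.46·0.54)/n).
- n = 1,200: s0 = 0.02021, s1 = 0.02017, power 84.4%.
- n = 1,020: s0 = 0.02192, s1 = 0.02188, power 78.2%.

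The pooled set meets the stated 80%. The screening-only set falls just short at the maximum exclusion: 1,068 per arm are needed, which corresponds to about 37% exclusions (1,700 x 0.63 = 1,071).

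**Step 2. False-positive rate if either test could be claimed.** The sets share 1,700/2,000 = 85% of men, so the arm-level results correlate at about √0.85 = 0.92. I simulated 200,000 null trials per setting, drawing Bin(1,020, 0.40) and Bin(180, p) in each of four arms and applying the 3-df chi-squared test (critical value 7.815) to both sets.

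| Survey men's rate p | Either test rejects |
|---|---|
| 40% | 6.9% |
| 55% | 6.8% |
| 70% | 6.3% |

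Two independent tests would give 1 − 0.95² = 9.75%. Letting the number of survey responders vary by chance between arms (before exclusions) gives 6.7 to 7.0%.

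**Step 3. How often the two tests disagree under an effect.**
- Arm rates 40/43/43/46%: 12.5 to 14.0% of trials.
- Arm rates 40/40/40/46%: 8.5 to 9.4% of trials.

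**Step 4. Ignoring survey status in the pooled test.** With 85% screening-only men at 40% and 15% survey men at p, the pooled rate is P = 0.85·0.40 + 0.15·p. The unstratified test uses variance P(1 − P); the within-stratum variance is 0.85·0.24 + 0.15·p(1 − p).
- p = 55%: P = 0.4225; 0.2411/0.2440 = 0.988.
- p = 70%: P = 0.445; 0.2355/0.2470 = 0.954.

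The true size of the pooled test is the probability that a 3-df chi-squared variable exceeds 7.815 divided by that ratio: 4.8% at p = 55% and 4.2% at p = 70% (simulation: 4.8%, and 4.2 to 4.3%). If the responder count varies by chance between arms, the size at 70% is about 4.5%. Stratifying restores about 5%.

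The power gain from stratifying is largest at p = 70%: from about 69.1% to 71.5% for 40/43/43/46, and from about 87.4% to 88.8% for 40/40/40/46. At p = 55% it is about 0.6 points for the first pattern. At p = 40% there is none.

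**The case against.** - **Only one test at 0.05 is specified.** A reader might infer that the trial tests its outcome twice at full alpha and wins on either. The article does not say so. It attaches no alpha to each set and states no such rule. The second analysis can fairly be read as a robustness check, and the 6.3 to 6.9% therefore applies only if either result could be claimed. What remains is that the article ranks neither analysis and powers both.
- **The choice of primary set can wait for the analysis plan.** Often so, and a commitment to produce both results limits selective reporting. But this article itself sets up two analyses of its primary outcome, so the point is an ambiguity it creates and not simply a detail left out.
- **Disagreement between nested sets is normal.** True of any sensitivity analysis. It does harm only when no rule says which result counts.
- **The pooled test is not wrong.** This stands. A reader might infer bias from ignoring survey status, but the planned split is the same in every arm and the baseline survey comes before any arm-specific letter. The cost is precision, and it is clear only at the assumed 70%. The covariate list is also open-ended, and the planned log-binomial models could hold survey status.
- **The pooled set does not contain the full randomised split.** Also correct: it holds about 300 responders to 1,700 per arm, not 600 to 1,700.

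**Conclusion.** The point holds as an unresolved decision rule with a modest cost. Two unranked analyses of the primary outcome sit beside a single test at 0.05. If either could be claimed, error rises by less than 2 points. The greater risk is the 9 to 14% chance, under the effects examined and with the same letter effect in both groups, that the two results conflict with no rule to settle it.

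Leaving survey status out of the pooled test is a loss of efficiency and not an error of validity. It makes the test mildly conservative and costs at most about 2.4 points of power, depending on a survey-group rate that the article does not give.

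The article does not support a claim of doubled error, of a stated rule that either result wins, or of a biased arm comparison. Nor does it make one set the only right choice: the pooled set is larger, the screening-only set is closer to programme conditions, and the sponsor may choose either.

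**What to change.** 1. State in one sentence which analysis is primary and carries the 0.05. Report the other as a prespecified sensitivity analysis.
2. Whenever survey men are included, stratify by survey group or put it in the model. Say that this stratum holds only baseline-survey responders, about 300 of the 600 randomised per arm.
3. Report the letter-by-survey-group interaction.
4. State the power that goes with the choice, pairwise and at the maximum 40% exclusion: about 84% if pooled, about 78% if screening-only.

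The cost is a sentence and one covariate, with no change to data collection or sample size. The downside is that the analysis not chosen becomes supportive. If both must stay confirmatory, each would need a level of about 0.036 to 0.037 to hold 5% overall given the overlap. Plain Bonferroni at 0.025 each would cut pairwise power to 76.7% (pooled) and 69.0% (screening-only).

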## Discussion

This project will identify whether recruitment strategies targeted to stage of readiness to screen, and the variables known to influence men’s movement to a higher stage, are effective in encouraging men to participate in FIT screening. The outcomes will provide information concerning how messages can be framed and delivered, in order to maximize participation in population screening programs in Australia and globally. If this study shows that a stage-matched intervention that addresses male concerns improves participation, the information may be useful for optimizing male participation in alternative forms of screening and preventive health practices. Future research incorporating a female population would be required to establish whether differences in participation result from the gendered information, or are a consequence of the overall improvements made to the screening invitation letters.

This study is among the first to dedicate a specific focus to understanding male screening behaviour. While several national screening initiatives exist for women in Australia (for example breast and cervical cancer screening programs) the NBCSP is the first nationally funded screening program to include men [7]. This study will collect extensive data on male attitudes toward screening through the use of quantitative surveys and qualitative interviews, and the results may also have important implications for future interventions.

A potential limitation of the study is that while the intervention aims to replicate the invitation protocol of the NBCSP, it will not be undertaken in collaboration with the national program. It is therefore likely that some of the participants invited to screen in this study may have recently participated, or are about to participate, in the NBCSP. To account for this potential limitation, participants will be encouraged to contact the research team when participation in other screening programs is the reason for declining the study offer. We acknowledge that this approach also has its limitations because it requires participants to actively volunteer the information to the research team, and because self-reported screening adherence can be inaccurate [46]. Consequently, participation rates observed in this study may be smaller than would occur for a population not exposed to other screening programs and will be considered in the reporting of results.

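### The stated 80% power for a 6-point difference is a figure for one unadjusted pair of arms; the only primary test named, the 2 x 4 chi-squared test, may have as little as 70% or 62%

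*Protocol article*

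**What the plan says.** Under Sample size considerations the article sets out two analysis sets, one "inclusive of survey participants (2,000 per trial arm") and one "exclusive of survey participants (1,700 per trial arm"), and says that both will be analysed. The power statement rests on two inputs. The first is the planning rate: "Assuming a participation rate of at least 40% for the control group". The second is the loss expected before analysis: "allowing for up to 40% of invited participants to be excluded due to being up to date with screening". From these it concludes that "these group sizes permit the detection of differential FOBT uptake of at least 6% between any two groups with at least 80% power". It does not say which test this power refers to.

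Under Statistical analyses, Primary outcome, one comparison is named: "A 2 x 4 (participation by intervention group) chi-squared test with alpha set at 0.05 will compare FIT participation rates between groups". Covariates are then to be checked with log binomial models. That section names no pairwise test, no test of either letter's main effect and no multiplicity rule.

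**The concern.** The power sentence and the analysis section describe different comparisons. The first promises power for a difference between two arms. The second tests equality of four arms on 3 degrees of freedom. A 6-point gap between two arms does not fix the power of the four-group test, because that also depends on where the other two arms lie.

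The stake is how a null result is read. If the 2 x 4 test is not significant, the published sentence invites the conclusion that a 6-point difference had at least an 80% chance of being found. In a factorial trial with two modestly effective letters, that could be wrong by 10 to 18 points of power.

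**Working it through.** **Inputs from the article.** Control rate 40% and difference 6 points, so 40% v 46%; alpha 0.05; 2,000 or 1,700 invited per arm; up to 40% excluded; equal allocation. Sidedness is not stated for the primary outcome. I assume two-sided, because a 3-df chi-squared test has no direction and the secondary analysis is described as two-tailed ("the ANCOVA using two-tailed significance will have 80% power").

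**Analysed numbers at 40% exclusion.** 2,000 x 0.6 = 1,200 per arm (inclusive). 1,700 x 0.6 = 1,020 per arm (screening only).

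**Step 1: reproduce the stated figure as one pair.** With p1 = 0.40, p2 = 0.46 and mean p = 0.43,

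power = Φ{ [0.06·√n − 1.96·√(2·p(1−p))] / √(p1(1−p1) + p2(1−p2)) }, where 2 x 0.43 x 0.57 = 0.4902 and 0.2400 + 0.2484 = 0.4884.

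- n = 1,200: Φ(1.011) = 84.4%
- n = 1,020: Φ(0.778) = 78.2%

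So the claim reproduces in the inclusive set and falls 1.8 points short in the screening-only set. Reaching 80% takes 1,068 analysed per arm. Unpooled and arcsine versions agree within 0.1 point; a continuity correction gives 83.4% and 77.2%. Solving for the difference that gives 80% power from a 40% control rate yields 5.66 points (n = 1,200) and 6.14 points (n = 1,020).

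**Step 2: the named 2 x 4 test.** Its power comes from the noncentral chi-squared distribution with 3 df, critical value 7.815 and noncentrality

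λ = n·Σ(p_i − p̄)² / [p̄(1 − p̄)].

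For a fixed largest gap, Σ(p_i − p̄)² is smallest when the other two arms lie midway. With 40/43/43/46%, p̄ = 0.43, Σ = 2 x 0.03² = 0.0018 and p̄(1 − p̄) = 0.2451.

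- n = 1,200: λ = 2.16/0.2451 = 8.81, power 70.1%
- n = 1,020: λ = 1.836/0.2451 = 7.49, power 62.2%

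Binomial simulation (400,000 runs) gave 70.1% and 62.3%.

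**Step 3: other patterns with the same 6-point largest gap.**

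| Arm rates (%) | n = 1,200 | n = 1,020 |
|---|---|---|
| 40/43/43/46 | 70.1% | 62.2% |
| 40/42/44/46 | 75.1% | 67.3% |
| 40/46/46/46 | 87.4% | 81.0% |
| 40/40/40/46 | 88.0% | 81.7% |
| 40/40/46/46 | 95.5% | 91.7% |

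The first two rows are what additive letter effects of 3 + 3 or 2 + 4 points would give.

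**Step 4: sensitivity to exclusions and control rate.** For the 2 x 4 test, 80% power needs λ = 10.90, so in the 40/43/43/46 pattern n = 10.90 x 0.2451/0.0018, about 1,485 analysed per arm. That is met only if exclusions stay below 1 − 1,485/2,000 = 26% (inclusive) or 1 − 1,485/1,700 = 13% (screening only). With no exclusions, power in this pattern is 91% and 86%. A control rate of 45% to 50%, which the plan's wording allows, lowers the 70% and 62% by about one point.

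**The case against.** The strongest defence is that the sentence is pairwise on its face. Read so, the inclusive set delivers 84% even at the maximum exclusion, and the screening-only shortfall is 1.8 points and disappears once exclusions are about 37% or less. All of that stands. The 78% alone would not be worth raising.

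A second defence is that 62% to 70% belongs to one pattern of arm rates at the exclusion ceiling, and that the 2 x 4 test has more than 80% when the arms sit at the extremes. This also stands, and it is why the point is that the test does not guarantee 80%, not that it never has it. But the unfavourable pattern is not contrived. The trial crosses two letters, and equal additive effects produce exactly that pattern, while the 40% exclusion is the plan's own allowance.

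Two stronger readings are tempting. One is that men who are up to date but do not report it stay in the denominator and dilute the difference. The Discussion concedes that the approach has limits because "it requires participants to actively volunteer the information to the research team". To turn this into a power loss, however, one must assume that the 40% control rate applies only to men who are not up to date, and the article does not say so. The Background reports 36.7% completion among all invited men in the national programme in 2008, so the planning rate may equally be a rate among everyone invited. The other reading is that power should be judged after adjustment for all six pairs, but the plan specifies no such procedure. Neither is supported, and neither is counted here.

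**Conclusion.** The concern holds in a limited form. The power sentence describes a comparison that the primary analysis does not name, and for the test that is named, 80% is not assured: 70% (inclusive) and 62% (screening only) when the largest gap is 6 points and the other two arms lie midway. A reader might infer that the stated power is simply wrong. The documents do not support that: as a single unadjusted pair it is met in the inclusive set (84%) and nearly met in the screening-only set (78%).

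These results assume a two-sided 0.05 level, a 40% control rate and the full 40% exclusion. With fewer exclusions every figure improves. The defect lies in what is claimed, not in the recruitment target.

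**What to change.** Restate the power sentence by test and by analysis set:

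- **Single unadjusted pair, control 40%, 40% excluded:** 80% power at about 5.7 points (inclusive) or just over 6.1 points (screening only).
- **2 x 4 test, same assumptions:** power for a largest gap of 6 points depends on the other two arms and may be as low as 70% (inclusive) or 62% (screening only).

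A main-effect figure should be quoted only if a main-effect analysis is added to the plan. Pooling two arms per level of a letter gives 2,400 v 2,400 or 2,040 v 2,040 analysed, and 80% power at about 4.0 or 4.3 points per letter.

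No extra men are needed. Screening had already ended in June 2013 according to Trial status, so this is a change to the text and to how a null result is reported. The cost is a less favourable power sentence.
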